## Abstract

The EISI study protocol aims to address the low participation rate in physical exercise programs among older individuals, emphasizing its significance as a non-pharmacological therapeutic approach for overall health and increased physical activity. The objectives include implementing physical activity (PA) and educational health programs in Jequié, Bahia, Brazil, targeting the Family Health Strategy population to enhance local physical activity levels among older individuals. The study also seeks to evaluate the program's feasibility, safety, and sustainability for large-scale implementation, along with assessing its impact on immune and inflammatory response biomarkers to the SARS-CoV virus, as well as physical-functional and brain health. Participants, aged 60 or above, will be divided into two groups: multicomponent exercise (MCE) and behavioral change interventions (BCI). The study employs a mixed-method approach, utilizing a non-randomized controlled short-term pathway model for a 4–8 weeks of pilot study and 16-week intervention impact assessment. Data collection encompasses various aspects such as sociodemographic information, mental health, physical fitness, fall risk, functional capacity, anthropometric measurements, hemodynamic assessment, habitual physical activity, and health-related quality of life. Blood and saliva samples are collected for cytokine and antibody biomarker analysis related to SARS-CoV immunity. Pre- and post-intervention evaluations for both groups will be conducted, with the hypothesis that MCE will yield more favorable responses compared to BCI. The study's holistic approach, including the assessment of feasibility, safety, and sustainability, aims to contribute to achieving Sustainable Development Goals (SDG) 3 and SDG 9 b y promoting accessible and sustainable healthcare initiatives for older individuals. This research aligns with global efforts to enhance health and well-being, emphasizing the importance of regular exercise in the aging population.

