### Study design

2.1

The EISI-SP will be a community intervention study, using a non-randomized controlled (nRCT), and short-term pathway model lasting 8–10 weeks [37], with two arms comprised physical exercise group versus control group with lifestyle behavioral change intervention. A pre- and post-design will be employed to assess the impact of the EISI program on several physical, metabolic, cognitive, and immunological function variables in the quantitative analysis. Additionally, a mix method of qualitative-quantitative approach will be conducted to evaluate the components of the RE-AIM model. This study protocol was developed based on the SPIRIT guidelines too [38].

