#### RE-AIM framework

2.6.4

This tool encompasses five dimensions, providing a comprehensive analysis of a health intervention's potential [32]. The Reach dimension indicates the number of potentially eligible participants for the intervention. The Efficacy/Effectiveness dimension quantifies the impact of the intervention, taking into account potential negative and positive effects. Adoption is related to the readiness of organizations and teams to initiate the program. Implementation assesses how well the proposed intervention can be applied to real-world conditions, considering planning, practices, costs, and established goals for execution. Lastly, the Maintenance dimension corresponds to the sustainability of a program over time [75].

Given this, the Reach indicators will include recruitment rates, participant characteristics, and participation rates in both the intervention. Efficacy/Effectiveness will encompass intervention group outcomes, including potential individual and collective benefits from the intervention program, as well as impacts on assessed health performances, adverse event rates, participant acceptability, and adherence. Adoption will incorporate quantitative and qualitative feedback on planning, execution, work environment(s), and team involvement. Implementation will evaluate the intended and actual duration of the intervention, proposed goals, any adaptations, as well as costs and user engagement levels. Maintenance will be assessed by both organizers and participants, considering the potential for sustained execution of the HEP and MEP programs over time.

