### Statistical data analysis

2.9

The assumption of normality was assessed using the Kolmogorov-Smirnov test with Lilliefors' significance correction, as well as through visual inspection of normality plots. For the specific case of comparing participants in the MEP intervention programs and comparison with HEP control group individuals, who were measured twice on the same variables at baseline and after 8 weeks of intervention, we will use either an independent T-test or Wilcoxon test, depending on data assumptions. Correlations will be calculated using Spearman's rank correlations.

To determine the effect sizes, the between-subject standard deviation for each dependent variable will be used to convert changes in all variables into standardized Cohen effect sizes (ES). Following Hopkins' guidelines, effect sizes will be categorized as trivial (d ≤ 0.2), small (0.2 < d < 0.6), moderate (0.6 < d < 1.2), large (1.2 < d < 2.0), very large (2.0 < d < 4.0), and nearly perfect (d > 4.0). This will be further confirmed by correlation matrices, where all variables in a group should correlate with at least 50 %, and principal component analyses, where the first component should account for at least 70 % of the variance.

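### Section 2.9 does not tie the labelled effect size to the MEP-minus-HEP difference in change; read literally, it labels before-after change, which does not answer the comparative hypothesis

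*Protocol article*

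**What the plan says.** The abstract states a comparative hypothesis, "with the hypothesis that MCE will yield more favorable responses compared to BCI". The methods sections call these two arms MEP (exercise) and HEP (the behaviour-change and health-education control). Section 2.1 describes a non-randomised controlled study "with two arms comprised physical exercise group versus control group with lifestyle behavioral change intervention". The same section adds: "A pre- and post-design will be employed to assess the impact of the EISI program".

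Section 2.9 names the comparison as "comparing participants in the MEP intervention programs and comparison with HEP control group individuals, who were measured twice on the same variables", and says of the test: "we will use either an independent T-test or Wilcoxon test, depending on data assumptions". It does not say whether the test is run on follow-up values or on change, or whether the Wilcoxon test is the rank-sum or the signed-rank version.

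The effect size is defined separately, in the next paragraph of 2.9: "the between-subject standard deviation for each dependent variable will be used to convert changes in all variables into standardized Cohen effect sizes". The bands start with "trivial (d ≤ 0.2), small (0.2 < d < 0.6), moderate (0.6 < d < 1.2" and continue to large, very large and nearly perfect (above 4.0). That paragraph mentions neither arm.

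Section 2.6.4, on RE-AIM, says that "Efficacy/Effectiveness will encompass intervention group outcomes, including potential individual and collective benefits from the intervention program". That sentence does not mention a contrast with HEP.

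**The concern.** The effect-size paragraph supplies a numerator (change in each variable), a denominator (between-subject SD) and a set of labels. An analyst who follows it word for word computes post minus pre over SD, and the pre-post wording of section 2.1 makes that reading easy to adopt. Any change that both arms share then goes into the labelled quantity: practice on the timed and cognitive tests, season, regression to the mean, or attention from the study team. Shared change is plausible here because HEP is an active programme. Section 2.6.2 describes sessions on physical activity, eating, social support and mental health, several of which are aimed at outcomes the trial measures.

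At stake are the magnitude statements. With about 20 people per arm, readers are likely to rely on the labels more than on the p-values. Two analysts could also report different labels from the same data, depending on which change they put in the numerator.

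**Working it through.** The article states no effect size, so there is no figure of the plan's own to reproduce. The check compares the two readings of the numerator.

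**Inputs from the article**
- 20 participants per group (section 2.2).
- Cut-points 0.2 and 0.6 (section 2.9).
- Two arms, each measured before and after (sections 2.1 and 2.9).

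**Assumed inputs (not in the article)**
- Shared change c of 0, 0.2, 0.3 or 0.5 SD in both arms.
- Pre-post correlation ρ of 0.5, 0.7 or 0.8.
- Baseline and follow-up SD of 1.
- No true difference between MEP and HEP.

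**Definitions**
- Own-arm reading: d = MEP change / SD, with expected value c.
- Between-arm reading: d = (MEP change − HEP change) / SD, with expected value 0.

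**Arithmetic at c = 0.3, ρ = 0.5, n = 20 (normal approximation, SD taken as known)**
- SE of the mean change in one arm = √(2(1 − ρ)/n) = √(1/20) = 0.224.
- P(own-arm d > 0.2) = P(Z > (0.2 − 0.3)/0.224) = P(Z > −0.447) = 0.67.
- SE of the difference in change = √2 × 0.224 = 0.316.
- P(between-arm d > 0.2) = P(Z > 0.2/0.316) = P(Z > 0.632) = 0.26.

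**Simulation (20,000 runs per setting, d scaled by the estimated pooled baseline SD)**

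| c | ρ | own-arm d > 0.2 | own-arm d > 0.6 | between-arm d > 0.2 |
|---|---|---|---|---|
| 0 | 0.5 | 19.6 % | 0.6 % | 26.7 % |
| 0.2 | 0.5 | 50.6 % | 4.5 % | 26.9 % |
| 0.3 | 0.5 | 67.3 % | 10.4 % | 26.4 % |
| 0.5 | 0.5 | 90.8 % | 34.0 % | 26.4 % |
| 0.3 | 0.7 | 71.9 % | 5.6 % | 21.0 % |
| 0.5 | 0.7 | 95.8 % | 30.1 % | 21.2 % |
| 0.3 | 0.8 | 76.0 % | 3.0 % | 16.5 % |
| 0.5 | 0.8 | 98.2 % | 27.2 % | 16.0 % |

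The simulation agrees with the hand calculation. The between-arm column does not move with c: its 16–27 % is sampling error alone. The own-arm column rises steeply with c.

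In the same simulations, an independent t-test on change scores rejected in about 5 % of trials at every setting. That shows that the test is protected from shared change. It is not the comparator for the 67 %, because one is a significance test and the other a band for a point estimate.

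**Example with a real difference.** If MEP changes by 0.8 SD and HEP by 0.5 SD, the own-arm reading gives d = 0.8, labelled moderate. The between-arm reading gives 0.8 − 0.5 = 0.3, labelled small.

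**The case against.** The strongest reply is that this is unspecified wording and not a stated error. Section 2.9 does not use the words own change or within-arm change. The paragraph just before the effect sizes sets up MEP against HEP with an independent-groups test, so the changes to be standardised could be differences in change. That test, if run on change scores, is not biased by shared change. The article is also condensed and may leave detail to a fuller plan. Much of this stands. It limits the point to the effect-size definition and makes it an ambiguity whose literal reading misleads. It does not remove the point, because the article does go as far as giving numerator, denominator and labels, and no HEP change appears among them.

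A reader might infer more: that the plan defines the effect of exercise as the MEP arm's own change, and that RE-AIM effectiveness leaves the control arm out, so shared change will be counted as benefit of exercise. The documents do not support that. No section says that within-arm change will be attributed to exercise. In 2.6.4 the verb encompass is not exclusive, and the sentence goes on to adverse events, acceptability and adherence, which are programme-level measures. The programme under evaluation includes both components: the introduction refers to exercise together with behaviour change, and 2.6.4 assesses maintenance of both HEP and MEP. An MEP-minus-HEP contrast is not the effectiveness of that combined programme.

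A reader might also quote rates of false significance from a paired test within MEP, or from comparing the two arms' labels. The article does not specify a paired t-test, leaves the Wilcoxon version open, and plans no comparison of labels, so such figures are not evidence about this plan.

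**Conclusion.** The point holds as a limited one. As written, the labelled effect size in section 2.9 is not tied to the between-group difference in change, and its literal reading does not answer the hypothesis. The planned between-group test is not affected if it is run on change scores.

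With no true difference, 20 per arm, ρ = 0.5 and a shared change of 0.3 SD, about 67 % of trials would carry an MEP label above trivial on the own-arm reading, against about 26 % on the between-arm reading. Across shared changes of 0.2 to 0.5 SD at that correlation, the own-arm figure runs from 51 % to 91 %. With no shared change it is 20 %, and the own-arm reading then does no harm. The size therefore rests entirely on the assumed shared change, which the article does not give.

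**What to change.** In section 2.9, define d as (MEP change minus HEP change) divided by the pooled baseline between-subject SD. Report it with a 95 % confidence interval and apply the magnitude labels only to that quantity. Show within-arm changes as description, without labels. Where RE-AIM effectiveness in section 2.6.4 makes a claim about MEP over HEP, use the same contrast; its programme-level measures can stay as they are.

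Baseline adjustment is not part of this request. Choosing between adjustment and change scores is contestable when allocation is not randomised. The new d removes change common to both arms, but it does not remove differences between self-selected or site-selected groups.

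The cost is wording, since both arms are already measured twice. Reported effect sizes will usually be smaller and less precise. At ρ = 0.5 and 20 per arm, the approximate 95 % half-width grows from 1.96 × 0.224 = 0.44 SD to 1.96 × 0.316 = 0.62 SD.

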**Fig. 1 fig1:**
[figure not shown]
**–** Timeline of the EISI study implementation.

A minimum sample size of 20 participants per group will be recruited, which is sufficient to detect significant changes considering a statistical effect size of p = 0.05, as established take into account previous similar study [42]. However, considering a predicted adherence rate of 70 % to the program, a minimum sample size of n = 24 for both the intervention and control groups is justified.

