#### Risk of falls

2.4.4

The risk of falls will be evaluated using three tests: i) a one question where participants will report if they had recent falls [49]; ii) the Timed Up and Go (TUG) test, measuring the time taken to rise from a chair, walk [50]; iii) and sit back down; and the 6-Meter Gait Speed Test, assessing walking speed. These tests will help identify individuals with a moderate risk of falls based on specific time cutoffs. Additionally, participants will have the option to choose between the 6-min walk test or the 2-min stationary march to evaluate aerobic endurance. The assessments require simple instruments such as a chair, measuring tape, and stopwatch, making them feasible for the study's participants [51].

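### The effect-size bands in section 2.9 are printed on signed d and use the point estimate alone, so every negative d is trivial as written, and chance alone often yields a small label at the planned size

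*Protocol article*

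**What the plan says.** Section 2.9 (Statistical data analysis) first names the group comparison: "we will use either an independent T-test or Wilcoxon test, depending on data assumptions". It then turns to magnitude: "the between-subject standard deviation for each dependent variable will be used to convert changes in all variables into standardized Cohen effect sizes (ES"). The banding rule follows: "effect sizes will be categorized as trivial (d ≤ 0.2), small (0.2 < d < 0.6), moderate (0.6 < d < 1.2), large (1.2 <", with two further bands above. The lowest band has an upper limit and no lower limit, and every other band is positive. No direction of benefit is given for any outcome, and the text does not say whether d is a between-group or a within-group quantity. The only confirmation named for the effect sizes is a set of correlation matrices and principal component analyses.

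The sample-size paragraph below Fig. 1 (section 2.2) states: "A minimum sample size of 20 participants per group will be recruited". After an allowance for adherence it adds that "a minimum sample size of n = 24 for both the intervention and control groups is justified".

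The outcomes point in different directions. Section 2.4.4 includes "the Timed Up and Go (TUG) test, measuring the time taken to rise from a chair, walk", where a shorter time is better. More positive SRQ-20 answers (2.4.2) and more points on the Functional Activities Questionnaire (2.4.5) are worse. A higher SPPB total (2.4.3) is better.

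**The concern.** A size label is useful if it separates effects that matter from those that do not, in both directions. This rule has two weaknesses.

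First, a band that takes in everything at or below 0.2 takes in every negative number. A change of d = -1.0 is *trivial* whether it is a clear gain on a timed test or a clear loss on a performance score. Section 2.6.4 says the effectiveness dimension of RE-AIM is to count negative as well as positive effects, and a rule with no band for negative values cannot do that.

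Second, the label depends on the observed d alone. If the sampling error of d exceeds the 0.2 limit, a *small* label says little about whether any effect exists. The trial has many outcomes, each of which would receive a label, so a results table could show a mix of sizes that reflects chance and sign convention more than the programme.

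**Working it through.** **Inputs.** From the article: 20 per group, raised to 24; the limits 0.2 and 0.6; changes divided by the between-subject SD. Assumed, because the article does not give them: normal data, equal groups, d taken between groups, the pooled baseline SD as standardiser, and a pre-post correlation r, shown from 0 to 0.9.

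**The plan's own figure.** The 20 per group cannot be reproduced. The article states no effect size, SD or power, and describes the 0.05 as an effect size ("sufficient to detect significant changes considering a statistical effect size of p = 0.05"). The sizes 20 and 24 are therefore used here as given.

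**Step 1, sign.** This needs no assumption. Any d < 0 satisfies d ≤ 0.2, so it is *trivial* as printed, whatever its size and whichever direction is beneficial.

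**Step 2, sampling error when the arms do not differ.** For post values, SE(d) = √(2/n).
- n = 20: √(2/20) = 0.316
- n = 24: √(2/24) = 0.289

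Both exceed 0.2.

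**Step 3, chance of *small* or larger with no true difference** (t distribution, 2n − 2 degrees of freedom).
- n = 20: 0.2/0.316 = 0.632. P(d > 0.2) = 0.265 and P(|d| > 0.2) = 0.531
- n = 24: 0.2/0.289 = 0.693. P(d > 0.2) = 0.246 and P(|d| > 0.2) = 0.492

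The chance of |d| > 0.6 (*moderate* or larger) is 0.065 at n = 20 and 0.043 at n = 24.

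**Step 4, changes over the between-subject SD.** SE(d) = √(2(1 − r) × 2/n). At r = 0.5 this equals √(2/n), so Step 3 carries over. The rates below come from simulation with 100,000 replicates.

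| Assumed r | SE, n = 20 | d > 0.2, n = 20 | abs(d) > 0.2, n = 20 | abs(d) > 0.2, n = 24 |
|---|---|---|---|---|
| 0 | 0.447 | 0.329 | 0.659 | 0.629 |
| 0.3 | 0.374 | 0.297 | 0.596 | 0.563 |
| 0.5 | 0.316 | 0.264 | 0.530 | 0.492 |
| 0.6 | 0.283 | 0.242 | 0.484 | 0.446 |
| 0.7 | 0.245 | 0.211 | 0.420 | 0.374 |
| 0.8 | 0.200 | 0.162 | 0.325 | 0.277 |
| 0.9 | 0.141 | 0.082 | 0.165 | 0.128 |

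If d were a within-group change instead, the |d| rate at n = 20 would be 0.38 at r = 0.5 and 0.17 at r = 0.8.

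**Step 5, label against test.** Two-sided 5% significance at n = 20 (38 degrees of freedom, critical value 2.02) needs |d| of at least 2.02 × 0.316 = 0.64 for post values or for changes at r = 0.5. The whole *small* band, 0.2 to 0.6, lies below that. At r = 0.8 the limit is 2.02 × 0.200, about 0.40, which falls inside the band.

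**The case against.** The strongest reply has four parts.

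- **Magnitude is the natural reading.** Bands of effect size usually refer to |d|, so the sign problem may be one of notation. That is plausible, but the text does not say so, and |d| alone still leaves the direction of benefit unstated. Under |d| the chance rate doubles, so this reading exchanges one weakness for the other.
- **A test is planned.** The label is not the only inference: the t-test or Wilcoxon test addresses chance. This is correct. However, section 2.9 does not connect the test to the label, and Step 5 shows that the two can routinely disagree. The confirmation it does name, correlations and principal components, does not measure the uncertainty of d.
- **Intervals may stand in a fuller plan.** That is possible for a journal article, and the absence of an interval is not by itself the finding. The finding is the rule as printed.
- **Small studies are imprecise anyway.** This is true, and it is why a label from the point estimate needs its interval beside it.

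A reader might infer something stronger: that the rule both hides all negative effects and labels about half of null outcomes *small* or larger. The document does not support that combination. Hiding negative values requires signed d, where the chance rate is about 26%. A rate near one half requires |d|, where negative values are not hidden, and for changes it also requires r of roughly 0.5 to 0.6, which the article does not give. Nor does the text support a calculation at 70% of 24, about 17 per group: "considering a predicted adherence rate of 70 % to the program" concerns adherence, which section 2.6.3 bases on sessions attended, not on loss from analysis.

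**Conclusion.** The point holds. The sign defect is certain from the text of section 2.9: as printed, every negative d is *trivial*, which mislabels large gains on lower-is-better outcomes and large losses on higher-is-better ones.

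The chance rate depends on the reading. With no true difference and 20 per group, *small* or larger appears about 26% of the time on signed d and about 53% on |d| (49% at 24 per group). Those figures apply to a between-group d on post values, or on changes with r = 0.5. For changes at 20 per group, the |d| rate falls from about 66% at r = 0 to about 17% at r = 0.9, so its exact size is not established by the article.

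The label should not be read as the trial's only evidence, since a test is planned beside it. It should be corrected because the rule is stated in full and misclassifies as it stands.

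**What to change.** In section 2.9:

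1. Define d as the MEP minus HEP difference in change divided by the between-subject SD, signed so that positive means benefit, and list the direction of benefit for each outcome.
2. Apply the bands to |d| and state the direction with each label. In the same edit, assign the exact values 0.6, 1.2, 2.0 and 4.0, which now fall in no band.
3. Report every d with its 95% confidence interval, and say that a label is to be read with the interval and is not evidence of an effect on its own.

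It is not necessary to require that the interval exclude zero before using the word *small*. At 20 per group (post values or r = 0.5) that would empty the band and turn the label into a repeat of the significance test.

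The cost is wording and one extra interval per outcome, with no new data. Some labels will look less favourable.

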The Intervention Study Protocol in Older Health (EISI-SP) aims to implement a physical exercise program for users of the Family Health Strategy in the municipality of Jequié, Bahia, Brazil, with the purpose of increasing LPA in the local population. As a secondary objective, this program will be assessed using the RE-AIM model to determine its feasibility and sustainability for large-scale implementation. Furthermore, at the end of the program, which will span 8 weeks of intervention with a multicomponent exercise and behavioral change approaches, the impact on several metabolic, immune, functional physical fitness, psychological well-being, and mental health indicators will be evaluated.

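### The correlation and PCA rule in section 2.9 cannot confirm an effect size, and the stated physical-activity purpose is never made a primary outcome among roughly 30

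*Protocol article*

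**What the plan says.** Section 2.9 (Statistical data analysis) compares the exercise and education groups with a t-test or Wilcoxon test. It then standardises the changes in all variables as Cohen effect sizes and grades them from trivial to nearly perfect. The next sentence sets two conditions: "This will be further confirmed by correlation matrices, where all variables in a group should correlate with at least 50" per cent, and "principal component analyses, where the first component should account for at least 70 % of the variance". It does not say what the 50 % measures, which variables form a group, or what follows if a condition fails.

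The Abstract states the hypothesis without naming a variable: "with the hypothesis that MCE will yield more favorable responses compared to BCI". The Introduction says the exercise programme is offered "with the purpose of increasing LPA in the local population" (LPA being the level of physical activity) and calls the RE-AIM evaluation a secondary objective. Section 2.4.8 measures activity with the IPAQ. No outcome is called primary anywhere. The sample size paragraph in section 2.2 (20 per group, raised to 24) is tied to no outcome.

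**The concern.** The word that opens the sentence in section 2.9 can only refer to the effect sizes and their grades, so the rule is presented as evidence that those effects are real. It cannot be. Outcomes that largely measure the same thing will correlate strongly whether or not the programme works. A real effect on an outcome unrelated to the others will fail. Followed as written, the rule would lend support to chance findings in redundant sets and withhold it from genuine findings on distinct outcomes.

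The missing primary outcome makes this worse. A general hypothesis of more favourable responses, spread over cognition, mental health, fitness, falls, function, body size, activity, quality of life and immune markers, can be declared supported by whichever result turns out well.

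**Working it through.** The two thresholds are criteria, not derived figures, so there is no plan figure to reproduce. Three checks apply.

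**1. Does the rule follow the effect?** Inputs: 20 per group (section 2.2) and the 50 % and 70 % thresholds (section 2.9). Assumed, because the article gives no values: four outcomes in a group, 50 % read as r = 0.5, a common correlation among outcomes, and a true d of 0 or 0.8 on every outcome. Each setting had 3,000 simulated trials. The rule passes if every pairwise correlation, pooled over arms, is at least 0.5 and the first component is at least 70 %.

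| Correlation among outcomes | Rule passes, d = 0 | Rule passes, d = 0.8 | t-test on one outcome significant, d = 0.8 |
|---|---|---|---|
| 0 | 0 % | 0 % | 69 % |
| 0.2 | 0 % | 0 % | 70 % |
| 0.5 | 7 % | 29 % | 71 % |
| 0.7 | 89 % | 97 % | 70 % |
| 0.85 | 100 % | 100 % | 69 % |

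Down each column, the pass rate runs from 0 to 100 % with the correlation. Across a row it moves far less. It rises with d at 0.5 and 0.7 because a shift shared by all outcomes adds some correlation when the arms are pooled. The t-test responds to d and hardly at all to the correlation.

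**2. How do the two thresholds relate?** If all k variables correlate at r, the first component's share is (1 + (k − 1)r)/k. If every correlation is at least r, this is the smallest share possible. For k = 3 and r = 0.5 it is (1 + 2 × 0.5)/3 = 0.667. Reading 50 % as shared variance gives r = √0.5 = 0.707, and for k = 3 a share of (1 + 2 × 0.707)/3 = 0.805.

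| k | Smallest share if r ≥ 0.5 | Smallest share if r² ≥ 0.5 | Common r needed for 70 % |
|---|---|---|---|
| 2 | 75.0 % | 85.4 % | 0.40 |
| 3 | 66.7 % | 80.5 % | 0.55 |
| 4 | 62.5 % | 78.0 % | 0.60 |
| 5 | 60.0 % | 76.6 % | 0.625 |
| 10 | 55.0 % | 73.6 % | 0.667 |

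On the first reading, three or more variables that only just meet the 50 % condition give a first component of at most 67 %, so the 70 % condition is the stricter one. On the second reading the share never falls below 70.7 %, so the 70 % condition adds nothing.

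**3. How many outcomes, and with what error rate?** Counted from sections 2.4.2 to 2.5.2: MMSE, SRQ-20, SPPB total, falls, TUG, 6-metre gait, aerobic test and Functional Activities Questionnaire (8); body mass and three circumferences (4); systolic and diastolic pressure, assumed from the sphygmomanometer (2); IPAQ activity and sitting time (2); two WHOQOL general items (2); three cytokines in serum and saliva (6); three immunoglobulins in serum and saliva (6). The total is 30, or 33 if the three SPPB tests are added.

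Taking 0.05 two-sided per test (sidedness is not stated), the chance of at least one false positive with independent tests is 1 − 0.95^30 = 0.785. It is 0.750 for 27 tests and 0.816 for 33. The expected number is 30 × 0.05 = 1.5. Simulation with 30 equally correlated test statistics gives about 0.66, 0.50 and 0.34 at correlations of 0.3, 0.5 and 0.7. With a single designated primary, the error for the primary claim is 0.05.

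**The case against.** The best defence is that the sentence reads like a criterion for grouping variables and may simply be misplaced. The article attaches no decision to it: no result is said to be promoted or dropped. That stands as a limit on the harm. It does not rescue the wording, which still offers the rule as confirmation of the effects.

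Four stronger readings are tempting, and the document does not support them.

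- A reader might infer that the two thresholds contradict each other. They are joint minimums, and data can meet both. With two variables, or with 50 % read as shared variance, the first condition already implies the second. The fault is that the 50 % and the groups are undefined.
- A reader might take the rule as the only check on the effects. Section 2.9 gives the t-test or Wilcoxon comparison first, and the rule is described as a further check.
- A reader might quote 0.785 as the false-positive risk. It requires independence, which is implausible for waist, hip and weight or for TUG and gait speed. The count of 30 is also a reconstruction, since no list of tested endpoints is given.
- A reader might call the absence of a multiplicity adjustment an error. That can be left to an analysis plan that is not shown here.

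On the primary outcome, it is fair to say that the Introduction ranks the aims to a degree, and that unranked estimation matters less in a pilot phase. What remains is that the stated purpose reaches neither the sample size nor the analysis.

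**Conclusion.** The point holds in two parts.

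First, the confirmation sentence in section 2.9 is wrong as written. Whether it passes is governed by the correlation among outcomes: 89 to 100 % with no effect at correlations of 0.7 to 0.85, and 0 % with d = 0.8 at correlations of 0 to 0.2. Those figures rest on the assumed four-outcome, equal-correlation setting and on r = 0.5. The conclusion does not, because shared variance among outcomes is not evidence of a group difference. The two thresholds differ in strictness according to the reading and the group size, and do not contradict each other.

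Second, roughly 30 outcomes are compared with none designated primary, despite a stated purpose that could supply one. The chance of at least one false positive ranges from 0.785 under independence down to about 0.34 at a common correlation of 0.7, well above 0.05 throughout.

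Both should be corrected. Neither shows that the trial's comparisons are invalid in themselves.

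**What to change.** In section 2.9, delete the sentence on further confirmation. Alternatively, recast it as a criterion for building composite scores from baseline data before any group comparison, stating whether 50 % means r or r-squared and which variables form each group. Report each standardised between-group difference with its 95 % confidence interval. A grade alone hides the uncertainty: at d = 0.6 with 20 per group the standard error is √(2/20 + 0.6²/80) = 0.323, so the interval runs from about −0.03 to 1.23, from trivial to large on the protocol's own scale.

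Carry the Introduction's purpose into section 2.9 by designating one physical-activity outcome from the IPAQ as primary. Weekly minutes is an example. Section 2.4.8 also classifies participants as active or not, so the sponsor should confirm the form. Label all other outcomes secondary or exploratory.

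The changes are to wording only and need no new data. The cost is that fewer results can be presented as confirmatory.
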